### 9.2.2 Secondary outcomes – individual level

One of the secondary aims to is to compare uptake by pathway, ethnic group, LSOA and age. This will be achieved using mixed-effect models with random effect for clusters (GP practice) with uptake regressed onto the predictor of interest while and adjusting the model for time. This will allow us to estimate the ICC and the time effect. We will use this approach to analyse the other binary secondary endpoints collected at individual level:

- The proportion of women who attend for follow up within 6m (cervical cytology, HPV primary test or colposcopy)
- The proportion with abnormal follow up results (cytology and/or HPV primary)
- The proportion with CIN2+ and CIN3+ on histology (also expressed as proportion of all women with a self-sample by age)
- The proportion of women whose self-sample is unavailable (insufficient DNA), and of these:
  - who return a second self-sample or attend for clinician sampling

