## 4 TRIAL DESIGN

A pragmatic implementation feasibility clinical trial of HPV self-sampling. The trial is designed to both test the pathway for implementing self-sampling within the NHS cervical screening programme in England and to estimate the associated increase in uptake and coverage. We anticipate that most GP practices invited will want to take part, however, the final number of GP practices included will depend on the recruitment and response rates of participants (as observed early on in the trial-set up).

Eligible women will be identified and offered self-sampling kits via two different pathways running in parallel:

- (i) **Direct mail-out (systematic offer)** - identified via NHAIS (national screening database) and kit posted to women's recorded home address, and
- (ii) **Opportunistic offer** – identified via electronic GP records and women offered kits when they consult GP primary care for any reason.

All participating GP practices will offer kits via both pathways.

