### 7.2.2 Opportunistic offering

Women targeted for opportunistic offering will be identified using the GP patient record software system (date of last recorded cervical screening test). Although cervical screening records in GP records are sometimes not up to date, this method of identifying the relevant cohort for opportunistic offering is currently the only viable option (GP patient records are not linked to the national screening database (NHAIS)).

An alert will be set up on the electronic patient record (EPR) software to automatically flag potentially eligible women when their record is opened. Specifically, EPR systems will be programmed to flag women aged 25.5-64 years who are at least 6 months overdue cervical screening (i.e. no cervical screening test (cytology, HPV primary or self-sample) recorded in the past 3.5 years (if aged 25-49) or 5.5 years (if aged 50-64) and no codes for hysterectomy or amputation of cervix). The alert will be switched on at the practice start date.

Doctors, nurses and healthcare assistants (HCA)/assistant practitioners (AP) will be asked to offer self-sampling kits to women who have been flagged when they consult for any reason. In practice, this will be on a case-by-case basis at the discretion of the healthcare professional consulted. The trial invitation (kit offer) will comprise a brief conversation (~2 minutes) at the end of the consultation. Healthcare professionals will be asked to confirm the women's eligibility before handing them a self-sampling kit, which includes the patient information booklet.

A study template will be set up in the GP electronic patient record system. When women are offered kits, the consulting health professional will use the template to record:

- 1) Whether or not the trial kit was accepted.

- 2) If accepted: trial kit ID number
- 3) If declined:
  - a) Reason for declining (if logistics allow)
  - b) Consent or dissent to share anonymous data from their GP records and the national cervical screening database

If the woman accepts a kit, the consulting health professional will:

- Print out a lab request/consent form with the woman's details mail-merged using the EPR system to be returned with the sample
- Write the kit ID number on the lab request/consent form
- Write three of the NHS CSP acceptable identifiers on the tube label. Preferably these will comprise the woman's name, date of birth and postcode.

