### 9.1.1 Direct Mail-out

Assuming 106 GP practices recruit women for an average of 9 months (GP practices will recruit for a minimum of 6 months and a maximum of 12 months given that study set-up at each practice will be staggered over a 6 month period) and 20 women reach the 15 month anniversary at each practice each month, approximately 19,000 women will be sent kits during the trial. Table 2 below provides the expected 95% confidence intervals for various uptake levels over an average of 9 months recruitment period. We have estimated that 15% of women who receive a kit via direct mail-out will return a self-sample (i.e. ~2,800 women will return a self-sample over an average of 9m).

**Table 2 Expected 95% confidence intervals for different proportions of women who return a self-sample based on 106 GP practices over a 9-month average recruitment period**

| Uptake among those offered kits | 95%CI     |
|---------------------------------|-----------|
| 10%                             | 9.6-10.4  |
| 15%                             | 14.5-15.5 |
| 20%                             | 19.4-20.6 |
| 30%                             | 29.3-30.7 |

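### The pathway comparison of uptake (section 9.2.2) is modelled with a practice random effect that, on its natural reading, assumes the same pathway odds ratio in every practice; if that ratio varies, the interval is too narrow.

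*Protocol*

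**What the plan says.** Uptake by mode of kit offer is a named secondary objective in the table in section 3.2. Section 9.2.2 sets out to "compare uptake by pathway, ethnic group, LSOA and age" and gives one method for all four predictors: "This will be achieved using mixed-effect models with random effect for clusters (GP practice) with uptake regressed onto the predictor of interest", with adjustment for time. It adds: "This will allow us to estimate the ICC and the time effect". No random pathway slope, practice-by-pathway effect or robust variance is named. Section 9.2 leaves the detailed description to a statistical analysis plan, which is not at hand.

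On the design, section 4 states: "All participating GP practices will offer kits via both pathways". The two routes work differently. Under section 7.2.1 a print company posts mail-out kits from a list drawn from the national screening database. Under section 7.2.2 practice staff offer opportunistic kits to flagged women, and: "In practice, this will be on a case-by-case basis at the discretion of the healthcare professional consulted".

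**The concern.** Because each practice contributes women to both pathways, a practice intercept shifts mail-out and opportunistic uptake by the same amount on the logit scale and largely cancels out of their difference. The model handles clustering in the overall level of uptake. For the pathway contrast it assumes a single log odds ratio shared by all practices, and any variation in that ratio between practices does not enter the standard error.

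The protocol's own description makes a shared ratio doubtful. Opportunistic uptake depends on staff, on the training format the practice chose (section 7.1.2) and on whether women sample on site (section 7.2.2). Mail-out uptake depends on these much less directly.

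The trial is set up to estimate rather than to test (section 9.1), so a trustworthy interval is part of what it delivers. The spread of the pathway difference across practices, which matters to anyone planning a wider roll-out, is not estimated by this model at all.

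**Working it through.** **Inputs from the protocol**
- Section 9.1.1: "Assuming 106 GP practices recruit women for an average of 9 months", and "20 women reach the 15 month anniversary at each practice each month, approximately 19,000 women will be sent kits during the trial". Also: "We have estimated that 15% of women who receive a kit via direct mail-out will return a self-sample".
- Section 9.1.2: 17,100 women offered a kit opportunistically, and 50% of those offered return a sample.

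**Reproducing the plan's figures.** 106 × 9 × 20 = 19,080, against the stated 19,000. At 15% uptake the simple binomial interval is 0.15 ± 1.96 × sqrt(0.15 × 0.85 / 19,080) = 14.5% to 15.5%, as in Table 2. The protocol states no interval, standard error or ICC for the pathway difference itself.

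**Standard error under a common odds ratio**
- Per practice: 19,080/106 = 180 mailed and 17,100/106 = 161.3 offered.
- Within-practice variance of the log odds ratio: v = 1/(180 × 0.15 × 0.85) + 1/(161.3 × 0.5 × 0.5) = 0.0436 + 0.0248 = 0.0684.
- Model standard error: sqrt(0.0684/106) = 0.0254.
- Log odds ratio: ln(0.50/0.50) − ln(0.15/0.85) = 1.735, an odds ratio of 5.67.

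**If the log odds ratio varies between practices with SD tau**
- True standard error: sqrt((v + tau²)/106).
- Ratio of true to reported: sqrt(1 + tau²/v).
- Actual coverage of a nominal 95% interval: 2Φ(1.96/ratio) − 1.

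| tau (assumed) | 95% of practices' odds ratios lie within a factor of | SE ratio | True SE | Actual coverage | Odds ratio interval with true SE |
|---|---|---|---|---|---|
| 0 | 1.0 | 1.00 | 0.0254 | 95% | 5.39–5.96 |
| 0.2 | 1.48 | 1.26 | 0.0320 | 88% | 5.32–6.03 |
| 0.3 | 1.80 | 1.52 | 0.0387 | 80% | 5.25–6.11 |
| 0.5 | 2.66 | 2.16 | 0.0548 | 64% | 5.09–6.31 |

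The factor is exp(1.96 × tau); the intervals are exp(1.735 ± 1.96 × SE).

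**The same in ICC terms (also assumed).** Give each pathway its own practice effects with ICC rho and correlation r between pathways. Then tau² = 2(1 − r) × [rho/(1 − rho)] × π²/3. With rho 0.05 and r 0.5, tau² = 0.173 and the ratio is 1.88. With rho 0.01 it is 1.40, 1.22 and 1.09 for r of 0, 0.5 and 0.8. With r = 1 it is 1.00 at any rho.

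**Simulation check.** A random-intercept logistic model was fitted to 106 simulated practices of equal size (300 runs per setting, intercept SD 0.3 assumed). The reported standard error stayed at about 0.0255 at every tau. The ratio of true to reported was 1.06, 1.27, 1.70, 1.96 and 3.02 at tau 0, 0.2, 0.3, 0.5 and 0.75. These scatter on both sides of the formula. What they confirm is that the reported standard error does not respond to tau while the true one does; the formula gives the steadier sizes.

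**A sparse outcome for contrast.** Section 7.5.3 expects 2% unavailable samples. About 2,800 mail-out and 8,500 opportunistic returns give 26.4 and 80.2 per practice. Then v = 1/(26.4 × 0.0196) + 1/(80.2 × 0.0196) ≈ 2.57, and at tau 0.5 the ratio is sqrt(1 + 0.25/2.57) = 1.05.

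**The case against.** The best defence is that the choice between a random intercept and a random slope is normally settled in the analysis plan. Section 9.2.2 covers four predictors and several outcomes in one generic sentence, and a pathway slope would also be a random effect for practice. That is true, and the wording does not forbid a slope. But it does state a method for this comparison and names a single ICC as its yield. A plan that follows it literally will fit an intercept only. This is a stated choice that fits the design poorly, rather than only an omitted detail.

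Three stronger readings are tempting, and the documents do not support them.

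- **That the interval is two to three times too narrow.** Ratios of 2 and 3 need tau of 0.45 and 0.74. The protocol gives no figure for tau, and the ratio could be close to 1.
- **That the protocol rules out a common odds ratio.** Staff discretion mainly decides who is offered a kit, and section 3.2 counts the opportunistic denominator from women recorded as offered. The pathways also share influences: letters go out on the practices' behalf and may carry GP endorsement (section 7.2.1), and one campaign serves both (section 7.2.3). These favour a positive correlation between a practice's two effects, which shrinks the problem.
- **That every outcome compared by pathway is affected to this degree.** The unavailable-sample calculation shows otherwise.

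It is also fair that the comparison is secondary and that no conclusion about direction is at risk: even at tau 0.7 the z value is about 24. The funnel plots and ICC in section 9.2.1 will show practice variation in uptake, but they do not correct the standard error of the pathway contrast.

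**Conclusion.** The point holds in a limited form. On its natural reading, the model in section 9.2.2 assumes one pathway odds ratio for uptake across all practices, and the two delivery routes make that unlikely. If the ratio varies, the interval for the average pathway difference in uptake is too narrow: by about 1.3 times at tau 0.2, 1.5 at 0.3 and 2.2 at 0.5, and not at all at tau 0.

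These sizes rest on the protocol's planning figures, on equal practice sizes and on assumed values of tau. The direction and significance of the expected contrast would not change, and sparse outcomes are little affected. What is at stake is the stated precision of a secondary estimate and the absence of any measure of how the pathway difference varies between practices.

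**What to change.** In section 9.2.2, or in the analysis plan that implements it, specify that when pathway is the predictor of uptake the model has a practice-level random slope for pathway in addition to the random intercept. Separate, correlated practice effects for mail-out and opportunistic offer are an equivalent form. If the model does not converge, use practice-clustered robust standard errors. Report the between-practice SD of the pathway log odds ratio beside the average contrast; under the slope model it can be estimated directly.

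The cost is one extra random term and a sentence of text, with no new data or participants. The downside is a wider interval if the difference varies between practices; if it does not, the interval should barely change.

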| Inclusion Criteria  | 
 
• Women <math>\geq 25</math> and <math>\leq 64^*</math> years old, and
 
• Eligible for cervical screening under the NHS CSP in England, and
 
• At least 6 months overdue cervical screening; and
 
• Registered at a participating GP practice
 
                                                                                                                                                                                                                                                                                                                                                                                                                                                                                         |                 |
| Exclusion Criteria  | 
 
• Women unable or unwilling to provide informed consent
 
• Women under the care of colposcopy within the last 36 months and/or due for a test of cure (HPV test to confirm if a woman has been successfully treated after treatment for cervical abnormalities)
 
                                                                                                                                                                                                                                                                                                                                                                                                                                                                                       |                 |
| Planned sample size | 
We expect up to ~10,000 women will return a self-sample
 
Assumptions:
 
 
• ~50% (106/212) of eligible GP practices recruited
 
• 9 months average recruitment period at GP practices
 
• An estimated 31,000 participants will receive self-sampling kits: 
 
○ 19,000 via direct mail out
 
○ 12,000 kits accepted opportunistically in GP primary care
 
 
 
• Estimated uptake: 15% for direct mail-out and 50% of those offered opportunistically
 
                                                                                                                                                                                                                       |                 |

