### 4.1 Trial set up

The trial is expected to be adopted onto the NIHR portfolio and will therefore have the support of the North Thames Clinical Research Network (NOCLOR) for identifying and setting up GP practices.

We anticipate that recruiting and setting up a large number of GP practices will be challenging. Therefore, we will take a pragmatic approach and have planned for a phased trial set up period over a target period of 3-6 months.

Given that the logistics required for setting up the opportunistic offer will be substantial (e.g. changes to the electronic patient record software, bespoke training to ensure optimal delivery of the intervention, kit supply) whereas direct mail-out can be easily initiated, it is likely that we will start the mailout almost immediately but stagger the opportunistic offer to align with the timing of activities required for site setup.

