### 9.1.2 Opportunistic offering of self-sampling

With an estimated 106 GP practices participating, there would be some 95,000 ( $190,579 \times (106/212)$ ) women eligible for opportunistic offering of kits. Based on our previous studies(16, 37)) we estimate that ~60% (57,000) will consult their GP practice over 9-12 months, some 17,100 (30%) will be offered a self-sampling kit and of those offered, ~12,000 (70%) will accept. We estimate that a total of ~8,500 would return a self-sample for HPV testing (50% of those offered i.e.  $17,000 \times 0.5$ ). Therefore, the proportion of women  $\geq 6m$  overdue cervical screening who will return a sample when opportunistically offered a kit (i.e.  $\approx 8,500/17,000$ ) could be estimated with a 95% confidence interval of width  $\pm 1.0\%$ .

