### 9.2.1 Primary endpoint

The primary outcome is uptake which is defined as the proportion of women who return a self-sample at 30 days, 90 days and at the end of the trial amongst those who have been given one direct mail out and opportunistic offer at GP practice with adjustment for multiple testing. We are interested in estimating variability across GP practice by using funnel plots(38) and estimating the intra cluster correlation (ICC).

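### The funnel plots, ICC, time effect and subgroup models for uptake pool two routes expected to give 15% and 50%, so where the route mix varies they partly measure that mix

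*Protocol*

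**What the plan says.** Section 3.2 defines uptake as women screened by self-sample divided by all women who were sent a kit or offered one opportunistically, so the denominator spans both routes.

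The two routes are expected to behave very differently: "Estimated uptake: 15% for direct mail-out and 50% of those offered opportunistically" (Trial Summary; repeated in 9.1.1 and 9.1.2).

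For this pooled uptake, section 9.2.1 plans "estimating variability across GP practice by using funnel plots(38) and estimating the intra cluster correlation (ICC", with no mention of route. Section 9.2.2 names pathway, ethnic group, LSOA and age as predictors and gives one model form for them: "mixed-effect models with random effect for clusters (GP practice) with uptake regressed onto the predictor of interest while and adjusting the model for time". It adds that the approach will yield the ICC and the time effect.

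On timing, section 4.1 says "it is likely that we will start the mailout almost immediately but stagger the opportunistic offer". Section 7.2.2 leaves each opportunistic offer to the clinician's judgement, case by case.

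The protocol does provide some results by route. Section 3.2 has a secondary endpoint comparing uptake between the two modes of offer, and defines uptake by ethnic group and LSOA both overall and by mode. Section 9.2 will tabulate primary and secondary outcomes overall and by pathway, and leaves the detailed analysis to the SAP.

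**The concern.** The funnel plots and ICC ask whether practices differ in response to self-sampling. The time effect asks the same of months, and the subgroup models of ethnic groups, areas and ages. A pooled proportion answers those questions only if the share of opportunistic offers is the same in every practice, month and group. With expected uptake 35 percentage points apart, that share moves pooled uptake strongly by itself.

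The protocol gives reasons to expect the share to vary. Offers depend on clinicians, and on which women consult. The opportunistic route is likely to start later than the mail-out. The mail-out reaches only women at the 15-month anniversary, while the opportunistic route takes any consulting woman at least 6 months overdue.

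A practice that simply makes more opportunistic offers could then be flagged as a high performer. The ICC, useful for planning wider roll-out, would absorb differences in mix. Uptake could seem to improve over the trial while neither route changed.

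**Working it through.** **Inputs from the protocol**

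- Mail-out (9.1.1): "20 women reach the 15 month anniversary at each practice each month, approximately 19,000 women will be sent kits during the trial"; expected uptake 15%.
- Opportunistic (9.1.2): "some 17,100 (30%) will be offered a self-sampling kit and of those offered, ~12,000 (70%) will accept"; expected uptake 50% of those offered.
- Practices recruit for 6 to 12 months, mean 9 (9.1.1).

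**The protocol's own figures reproduce**

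- Mail-out: 106 × 9 × 20 = 19,080 kits, or 180 per practice; × 0.15 = 2,862 returns. The 95% interval 0.15 ± 1.96 × √(0.15 × 0.85 / 19,080) is 14.49% to 15.51%, against 14.5–15.5 in Table 2.
- Opportunistic: 95,290 × 0.6 × 0.3 = 17,152 offered, about 161 per practice; × 0.5 = 8,576 returns.
- Pooled uptake per practice: (180 × 0.15 + 161 × 0.50) / 341 = 107.5 / 341 = 31.5%.

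**Funnel plot by hand**, with true uptake exactly 15% and 50% in every practice

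- Funnel standard error: √(0.315 × 0.685 / 341) = 0.0252.
- True sampling SD at fixed mix: √(180 × 0.1275 + 161 × 0.25) / 341 = 0.0233. With equal mix, P(|Z| > 1.96 × 0.0252 / 0.0233) is about 3.4%: slightly conservative, no false signal.
- If opportunistic offers vary with coefficient of variation (CV) 0.3, their SD is 0.3 × 161 = 48.3. The change in pooled uptake per extra offer is 0.35 × 180 / 341² = 0.000542, so mix adds an SD of 0.0262.
- Total SD: √(0.0233² + 0.0262²) = 0.0351, which is 1.39 funnel standard errors. P(|Z| > 1.96 / 1.39) is about 16%.

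**Funnel plot and ICC by simulation**, 106 practices, same null. The CVs are assumptions; the protocol gives none.

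| Route mix | Outside 95% limits, pooled | ICC, pooled (ANOVA; logistic latent scale) |
|---|---|---|
| Equal in every practice | 3.4% | about 0 |
| Both routes start together, 6–12 months | 3.3% | about 0 |
| CV 0.1 | 5.6% | 0.0002; 0.0003 |
| CV 0.3 | 16% | 0.003; 0.004 |
| CV 0.5 | 32% | 0.008; 0.011 |
| CV 0.8 | 50% | 0.018; 0.029 |
| Mail-out 12 months, opportunistic 6–12 months | 11% | 0.001; 0.002 |

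Allowing for route brings the share outside to 4.6–5.0% and the latent ICC to 0.0004 or less in every row.

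**Time effect.** Scenario: mail-out of 20 a month throughout; 18 opportunistic offers a month, starting in months 1 to 7 with equal probability.

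- Month 1, one practice in seven offering: (3 + 9/7) / (20 + 18/7) = 19.0%.
- Month 7 onwards: (3 + 9) / 38 = 31.6%. Neither route has changed.
- A random-intercept logistic model with time only gave an odds ratio of 1.81 over 12 months and rejected in all 40 simulated trials. With a pathway term the odds ratio was 1.00, with rejection in 1 of 40 (2.5%).

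**Ethnic group.** Scenario: 30% of women in one group, whose opportunistic share is 10 points higher (54.2% v 44.2%; an assumption).

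- Pooled uptake: 0.15 + 0.35 × 0.542 = 34.0%, against 0.15 + 0.35 × 0.442 = 30.5%; odds ratio 1.17.
- Over 60 simulated trials per scenario, differences of 0, 2, 5 and 10 points rejected in 7%, 23%, 92% and 100%. With a pathway term: 3–8%.

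**The case against.** **Covariates and funnel layout belong in the SAP, which is not shown.** This has weight for 9.2.1, which only expresses an interest in practice variability. It has less for 9.2.2, which states a model form; an SAP that follows it inherits the omission.

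**The protocol already reports by route.** This stands in part. A reader might infer that the inequality conclusion is simply misdirected. The documents do not support that, because section 3.2 gives ethnicity and LSOA uptake by mode of offer. Those provisions do not change the 9.2.2 model, and none supplies a route-specific model or plot for age, time, the funnel plots or the ICC.

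**Pathway is one of the listed predictors.** True: that model contains pathway, practice and time, so its ICC and time effect are conditional on route. The protocol does not say that those are the ones to be reported, and the other three models remain without pathway.

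**The timing is tentative.** Section 4.1 says only that a staggered opportunistic start is likely. Section 7.2.1 admits practices to the mail-out after training, so mail-out entry may be staggered too. Time is not defined. If both routes start together in each practice, the funnel distortion disappears. This makes the finding conditional.

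**Overall uptake is a legitimate quantity in a pragmatic trial in which every practice uses both routes.** Agreed. Which route reaches a group is part of the programme's effect, and section 3.2 asks for the overall figure. It should stay, beside the route-adjusted one.

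**Conclusion.** The point holds, conditionally. As written, the practice, time and subgroup analyses of uptake mix response to self-sampling with the share of opportunistic offers. The 15% and 50% are the protocol's own figures, and its discretionary, probably staggered opportunistic offer makes a varying share likely.

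The time effect is best supported, because the stagger is described in the document: a false odds ratio of about 1.8 over 12 months in the scenario tested, with the same kind of stagger alone putting about 11% of practices outside 95% limits. The 16% to 50% of practices outside, and the ICC of about 0.003 to 0.03, rest on assumed CVs of 0.3 to 0.8. In absolute terms the ICC inflation is small. The ethnicity figures rest on assumed differences in opportunistic share that the protocol does not quantify. All the calculations treat the two routes as separate groups of women.

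A reader might infer that these analyses give false signals whenever uptake within each route is identical. They do not: with equal mix the pooled funnel is slightly conservative and the ICC is near zero. Nor do funnel plots and ICCs reject a hypothesis; they flag practices or become inflated. The point is worth correcting but does not undermine the estimates of uptake by route.

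**What to change.** - **Section 9.2.1:** draw funnel plots and estimate the ICC separately for mail-out and opportunistic uptake, or standardise both for route.
- **Section 9.2.2:** add a pathway term to the ethnicity, LSOA and age models and to the model from which the time effect is reported. Keep the overall, unadjusted estimates that section 3.2 asks for alongside. Pathway-by-predictor terms are optional: in the checks, a pathway term alone brought rejection close to the nominal rate.
- **Attribution rule:** section 7.2.2 allows a woman to be mailed a kit and also offered one at her practice. Section 7.4 codes the source only for returned samples, so a woman reached by both routes who returns nothing has no single pathway. State one rule that uses information available for returners and non-returners alike, such as mailing dates and the offers coded in GP records.

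The cost is a wording change in 9.2 carried into the SAP, with no new data collection. The downside is two funnel plots and two ICCs, each on about half the women (19,080 mailed and about 17,150 offered), plus the work of settling the rule.
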